**Mesocycle 1 and 2**								
	**Day 1**							
		Bike	4		120		30	
		Sandbag lift and carry	2		240		60	
		Reverse lunges alternate legs	7		20		30	
	**Day 2**							
		Rope slams (slow cadence)	10		30		30	
		Farmer’s walk (speed walk)	2		240		60	
		Kettlebell high pulls	7		20		30	
	**Day 3**							
		Bike	3		180		60	
		Side to side step ups to box	10		30		30	
		Triceps dips	7		20		30	
**Mesocycle 3**								
	**Day 1**							
		Bike with resistance	5		90		30	
		Sandbag shoulder to shoulder	10		30		20	
		Ladders forward and backward	5		20		60	
	**Day 2**							
		Rope slams	5		20		50	
		Sandbag carry walk	3		150		60	
		Suspension trainer rows	10		30		30	
	**Day 3**							
		Run	2		240		120	
		Push-ups (Suspension trainer)	10		30		30	
		Side-to-side jumps	5		20		60	
**Mesocycle 4**								
	**Day 1**							
		Sprint (20 m)	10		N/A^a^		30	
		Farmer’s carries	15		5		30	
		Skater jumps	10		30		30	
	**Day 2**							
		Weighted vest jog	3		60		120	
		Ropes (drumming)	9		20		45	
		Suspension trainer rows (overhand grip)	10		30		30	
	**Day 3**							
		Jog	1		480		120	
		Push ups	10		30		30	
		Scissor jumps	10		10		45	

^a^N/A: not applicable.

**Table 7 table7:** Summary of high-intensity interval training blocks.

Mesocycle, day, and goal for the session				Target HR^a^ (% maximum HR)
**Mesocycle 1 and 2**				
	**Day 1: aerobic power**			
		Week 1	75	
		Week 2	80	
		Week 3	85	
	**Day 2: upper-body localized anaerobic power**			
		Week 1	75	
		Week 2	80	
		Week 3	85	
	**Day 3: cardiac output**			
		Week 1	65	
		Week 2	70	
		Week 3	75	
**Mesocycle 3**				
	**Day 1: lower-body** **anaerobic power**			
		Week 1	80	
		Week 2	85	
		Week 3	90	
	**Day 2: upper-body localized anaerobic power**			
		Week 1	80	
		Week 2	85	
		Week 3	90	
	**Day 3: aerobic maintenance**			
		Week 1	65	
		Week 2	70	
		Week 3	75	
**Mesocycle 4**				
	**Day 1: lower-body anaerobic power**			
		Week 1	85	
		Week 2	90	
		Week 3	95	
	**Day 2: upper-body localized anaerobic power**			
		Week 1	80	
		Week 2	85	
		Week 3	90	
	**Day 3: aerobic maintenance**			
		Week 1	65	
		Week 2	70	
		Week 3	75	

^a^HR: heart rate.

#### Exercise Logs

Participants in both groups will be provided with a log to record the exercises performed outside of the supervised study training. Participants will record RPE, exercise type, duration, setting (eg, home or gym), date, and how the session felt. Exercise will be described to participants as a specific form of physical activity that is planned and structured and includes intentional movements intended to improve or maintain physical fitness. An RPE scale will be provided, and participants will select a number between 1 and 10 to express their RPE, ranging from very light (1-2) to maximum effort (9-10). The control group will record all the exercises performed during the 18-week study period. The intervention group will record the core reconnection training sessions as a metric of compliance and any other exercise in addition to the physical development training sessions performed during the study period.

#### Intervention Compliance (Intervention Group Only)

Compliance with weekly core reconnection training will be checked verbally and by using exercise logs. A participant who misses >25% (>3/12) of sessions over 2 consecutive weeks or who fails to achieve at least two of the three supervised physical development training sessions over 2 consecutive weeks, will be approached by one of the research team members to understand the reason for low compliance. These participants will be given an opportunity to increase their participation rate over the following week, if appropriate. Failure to increase participation during this week will result in a participant being considered noncompliant. Before recruitment, participants will be made aware of noncompliance thresholds. Cases of noncompliance will be reported to a trial committee that will attempt to contact the participant before deciding to exclude the individual from further participation in the trial.

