### Intervention

#### Overview

The control group will receive standard postpartum care only, which consists of a 6-week postpartum check at a civilian general practice or a Defence primary health care facility and referral to (1) secondary care pelvic health physiotherapy if women present with symptoms of urinary incontinence and (2) musculoskeletal physiotherapy if they present with *rectus diastasis* or a musculoskeletal injury. Control participants will not be prescribed exercises but will not be prevented from choosing to exercise during the study period. A log of all exercise activities will be collected from control participants. The intervention group will receive standard postpartum care and complete a phased 18-week combined rehabilitation and physical development program. The rehabilitation element of the program was designed for this study by specialist pelvic health physiotherapists. The program, known collectively as *core reconnection training*, targets pelvic floor function and pelvic, hip, and abdominal strength. The *physical development training* is an adapted version of the SPARTA (Soldier Performance and Readiness as Tactical Athletes) training program [37] and consists of resistance training and HIIT.

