#### Core Reconnection Training

Following testing session 1, participants in the intervention group will commence 18 weeks of home-based core reconnection training from weeks 6 to 24 post partum (Table 1). Participants will complete 3 core reconnection training sessions per week, each lasting approximately 30 minutes. Each session will include 6 exercises progressing in difficulty throughout the intervention. Participants will complete 3 to 4 sets of 8 to 12 repetitions of each exercise. Participants will be advised to reduce the number of repetitions of more challenging exercises (eg, press-ups) to 3 to 4 sets of 5 repetitions. Exercises will be modifiable depending on individual ability and symptoms. Participants will be advised to be aware of symptoms of incontinence, a heaviness or dragging sensation in the pelvic area (ie, indicator of prolapse), a pendular abdomen or noticeable gap in the midline of the abdominal wall (ie, indicator of *rectus diastasis*), and pelvic or lower back pain. If any of these symptoms are experienced, participants will be asked to contact the study’s pelvic health physiotherapist before continuing with training. Participants will be given written instructions with images of each exercise and will be provided with access to all exercises in video form with verbal instructions. Core reconnection training sessions will not be routinely supervised.

**Table 1 table1:** Core reconnection training.

	Exercise 1	Exercise 2	Exercise 3	Exercise 4	Exercise 5	Exercise 6
Week 1	Arm circles + heel slide	Glute bridge + squeeze	Side kick	Bent knee fall out	Toe slide all fours	Tempo squat to chair
Week 2	Toe taps + arms	Glute bridge + band pull	Side kick straight leg	Eccentric curl down	Toe slide + arm slide	Tempo squat to chair
Week 3	Arm circles + heel slide in tabletop	Single-leg glute bridge	Sidestep + band	Abdominal prep	Superman	Squat to tip toes
Week 4	Running man	Monster walk + band	Mountain climber	Eccentric curl down + rotation	Superman knee to elbow	Static lunge + arms overhead
Week 5	Knee pull	Banded deadlift	Mountain climber knee to elbow	Oblique prep	All four hover	Lunge + rotation band pull
Week 6	Single-leg squat + rotation	Banded deadlift	Mountain climber (increased pace)	Russian twist	Bear crawl	Lunge + rotation band pull
Week 7	Opposite knee to elbow in standing	Single-leg deadlift	Press-up to chair	Side-lying double-leg lifts	Plank to pike	Lateral lunge

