### Primary Outcome Measures

#### Occupational Physical Performance Overview

Occupational physical performance will be measured at weeks 12 and 24 using the Role Fitness Test (Entry), which is used by the British Army as a selection standard to confirm the appropriate level of fitness to commence basic training. It involves an isometric mid-thigh pull, seated medicine ball throw, and a timed 2-km run. A vertical jump test will be completed as a military-relevant field-based measure of power. The occupational physical performance tests will be conducted using military equipment and following military procedures (field-expedient measures). As part of military physical performance testing, there is a minimum standard that individuals must achieve, and maximum scores or values are used across these tests. The maximum values will be reported for the occupational physical performance tests in this study.

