### Power Calculation

Kraemer et al [62] identified that single-lift strength was 39 (SD 7) kg and 37 (SD 5) kg for women at the end of a 6-month total strength and power and total strength and hypertrophy resistance training protocol, respectively, compared with 32 (SD 4) kg for women undertaking normal field-based military training. Based on the effect sizes between these training and control groups (total strength and power vs control, Cohen *d*=1.23; total strength and hypertrophy vs control, Cohen *d*=1.10), it is anticipated that between 9 and 11 women would be required per group to identify greater posttraining strength in the intervention group than in the control group, with a 1 − β of .80 and α of .05. Hendrickson et al [63] identified that squat and bench press 1 RM were 77 (SD 3) kg and 41 (SD 2) kg, respectively, for women at the end of a 12-week endurance and strength training program, compared with 68 (SD 4) kg and 34 (SD 2) kg for women in the control group, respectively. Based on the effect sizes between the training and control groups (squat, Cohen *d*=2.55; bench press, Cohen *d*=1.62), it is anticipated that between three and six women would be required per group to identify greater posttraining strength in the intervention group than in the control group, with a 1 − β of .80 and α of .05. Hendrickson et al [63], identified that a 3.2-km run time was 18.5 (SD 1.0) minutes for women at the end of a 12-week combined endurance and strength training program, compared with 22.1 (SD 1.2) minutes for women in the control group. Based on the effect sizes between the training and control groups (Cohen *d*=3.26), it is anticipated that 3 women would be required per group to identify greater aerobic fitness in the intervention group than in the control group, with a 1 − β of .80 and α of .05. As such, 11 participants per group would be sufficient to detect improved strength and aerobic fitness in the intervention group compared with the control group. To allow for dropout and noncompliance, we aim to recruit a minimum of 15 participants per group.

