### Statistical Analysis

To maximize statistical power, outcomes will be analyzed using mixed-effects linear models to leverage the collection of data on more than 2 time points and to facilitate the analysis of unbalanced data based on participant attrition. Participants will be included as random effects, with group and time included as fixed effects, to assess within- and between-group differences over time. Sensitivity analyses will be conducted by including baseline values in models or other data relative to potential confounders to account for nonrandom allocation. Linear models will be structured to assess within- and between-group differences over time (eg, the inclusion of resistance and HIIT exercise), establishing the rate of change of intervention and control and determining whether these rates are distinct. The suitability of the models will be established by assessing model residuals and transformations made if residuals are not normally distributed or homoscedastic. Uncertainty in parameter estimates will be quantified using the Satterthwaite approximation for *df* values or through bootstrapping procedures. To facilitate interpretation of the magnitude of change across different outcomes, analyses will be standardized relative to the baseline SD, thus placing outcomes on a unitless scale. Principal component analysis will be conducted on change scores to investigate the clustering of outcomes relative to the magnitude of change.

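### Noncompliant women can be excluded from the trial in the intervention group only, with no provision to test them at week 24, so post-allocation loss may favour the program

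*Protocol article*

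**What the plan says.** - **The rule (Intervention Compliance).** The section heading limits it to the intervention group. A woman below the attendance thresholds is approached and, where appropriate, given a week to improve. Then: "Failure to increase participation during this week will result in a participant being considered noncompliant". Such cases go to a trial committee, which tries to reach the woman "before deciding to exclude the individual from further participation in the trial". The exclusion is worded as from the trial, not only from training.
- **Controls (Intervention, Overview).** "Control participants will not be prescribed exercises but will not be prevented from choosing to exercise during the study period". They have no attendance threshold to fail.
- **Timing.** Training subject to the rule starts at week 6: "participants in the intervention group will commence 18 weeks of home-based core reconnection training from weeks 6 to 24 post partum". The primary outcome comes later: "Occupational physical performance will be measured at weeks 12 and 24 using the Role Fitness Test (Entry").
- **Sample size (Power Calculation).** Eleven per group are held to be sufficient. "To allow for dropout and noncompliance, we aim to recruit a minimum of 15 participants per group".
- **Analysis (Statistical Analysis).** Mixed models with participant as random effect and group and time as fixed effects are chosen partly "to facilitate the analysis of unbalanced data based on participant attrition". The sensitivity analyses named there address nonrandom allocation, not exclusion after allocation.

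No section says that an excluded woman will still be invited to the remaining tests.

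**The concern.** A removal rule that operates in one arm after allocation can make the arms differ for reasons unrelated to the program. The document itself makes a link between compliance and outcome plausible. Under Core Reconnection Training, women with incontinence, heaviness, or pelvic or back pain are asked to contact the physiotherapist before continuing. Women recovering slowly may therefore both miss sessions and perform worse at week 24. If they leave the intervention arm while similar controls stay, the intervention mean is flattered.

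This would add to the confounding already possible from allocation by location. It also moves the estimate away from the question the Dissemination Policy raises. The program is meant to be offered to servicewomen after childbirth in general, and some of them will comply poorly.

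**Working it through.** **1. The plan's own figure.** One-sided α of 0.05, 80% power, two means: n per group = 2(1.645 + 0.842)²/d² = 12.37/d².
- d = 1.23: 8.2, so 9.
- d = 1.10: 10.2, so 11.

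Both match the stated 9 to 11. The protocol does not state sidedness; the two-sided formula gives 11 and 13. Going from 11 to 15 allows for a loss of 4/15 = 26.7% per group, since 11/(1 − 4/15) = 15. That allowance covers dropout and noncompliance together.

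**2. Inputs the documents do not give.** Both are assumed: the number of women excluded (1 to 4 of 15, with 4 as the upper case because it spends the whole allowance on noncompliance) and the correlation r between compliance and week-24 outcome (0.3 to 0.5). No true effect is assumed throughout.

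**3. Raw week-24 comparison.** If the least compliant fraction f is removed, the retained mean shifts by r × φ(z_f)/(1 − f) SD, where z_f is the normal quantile at f. For f = 4/15, φ(z_f) = 0.329 and 0.329/0.733 = 0.448.

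| Excluded of 15 | r = 0 | r = 0.3 | r = 0.5 |
|---|---|---|---|
| 1 | 0 | 0.04 | 0.07 |
| 2 | 0 | 0.07 | 0.12 |
| 3 | 0 | 0.10 | 0.17 |
| 4 | 0 | 0.13 | 0.22 |

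Simulating 40,000 trials with 15 controls and 11 retained trainees gives 0.13 SD (r = 0.3) and 0.21 SD (r = 0.5). The one-sided 5% test then rejects about 9% and 13% of the time, and the two-sided test about 6% and 8%.

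**4. Closer to the planned analysis.** A likelihood analysis keeps the week-12 value of a woman excluded later. Her group's week-24 mean is estimated as the completers' mean plus the pooled within-group slope times the difference in week-12 means between all women and completers. Groups are compared on change. With 4 of 15 excluded, all of them having week-12 data, the bias in SD over 20,000 trials per cell is:

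| What exclusion tracks | Week 12–24 correlation | r = 0.3 | r = 0.5 |
|---|---|---|---|
| Stable fitness | 0.70 | 0.04 | 0.06 |
| Stable fitness | 0.85 | 0.02 | 0.03 |
| Later response not predicted by week 12 | 0.70 | 0.09 | 0.15 |
| Later response not predicted by week 12 | 0.85 | 0.07 | 0.11 |

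In the last two rows r is the correlation with the unpredicted part of the week-24 value. If exclusion depended only on the observed week-12 value, the bias would be about zero. If the week 12–24 correlation were as low as 0.6, the upper end would be about 0.17.

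**5. What the model cannot use.** A woman excluded between weeks 6 and 12 has no primary-outcome value at all. One excluded later has a single value, taken before supervised training starts.

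**The case against.** - **Exclusion is discretionary.** It follows an approach, a chance to improve and an attempt at contact, and the committee may keep a noncompliant woman. A reader might infer that the week-24 comparison will set compliant trainees against all controls. The text does not support that: it permits exclusion but does not require it, and the loss allowance applies to both groups, so controls may drop out too. What remains is that only trainees can be removed by rule.
- **The direction is not certain.** Bias is zero if compliance is unrelated to outcome, and it reverses if fitter or busier women skip sessions. This stands.
- **The raw comparison is not the planned analysis.** This also stands. Keeping week-12 data cuts the bias substantially when exclusion tracks stable fitness. If, in addition, two of the four losses are random dropouts and four controls are lost, it falls to 0.01 to 0.03 SD. The mixed model is still only a partial answer: it assumes missing values are explained by what it contains, and compliance is not in it.
- **Inflating for noncompliance does not prove the data will be missing.** Inflation can also offset dilution. Agreed; the point rests on the wording about further participation in the trial and on the absence of any provision for continued testing.
- **Analysis populations may be set in an analysis plan not shown.** Fair, and their absence is not the complaint. Whether women are tested after noncompliance is a protocol matter, and an analysis plan cannot supply data that were never collected.

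**Conclusion.** The concern holds as a moderate one. As written, the protocol allows loss of week-24 primary data after allocation in the intervention arm only, and that loss would be expected, though not certain, to favour the program. Under no true effect, r of 0.3 to 0.5 and the upper case of 4 of 15 excluded, the bias is about 0.13 to 0.21 SD in a raw comparison. It is about 0.02 to 0.15 SD in a likelihood analysis keeping week-12 data, with an assumed week 12–24 correlation of 0.70 to 0.85. The position within that range depends on whether exclusion tracks stable fitness or unobserved later response. The exclusion rate and both correlations are assumptions.

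Against planned strength effects of d = 1.10 or more, this would not by itself produce an effect of the size expected. A reader might conclude that the rule guarantees a positive result or invalidates the trial; neither follows. It should be fixed because the distortion is avoidable, adds to the confounding from nonrandom allocation, and cannot be repaired once the tests are missed.

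**What to change.** Replace exclusion from the trial with: *Noncompliant participants will be invited to all remaining testing sessions, and all enrolled participants will be analysed in the group set by their location of care.* Use the compliance threshold only to define a secondary per-protocol analysis. Whether a woman continues training stays with the trial committee.

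The cost is one protocol sentence and one analysis sentence; the visits are already planned. Because recruitment began in 2019 and participants are told the thresholds beforehand, the information given to them would need to match. The estimated effect may be smaller, and some women who have stopped training may decline the visits. If all 15 per group are retained, power at d = 1.10 is about 90% one-sided or 83% two-sided, before any dilution from noncompliance.

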### Primary Outcome Measures

#### Occupational Physical Performance Overview

Occupational physical performance will be measured at weeks 12 and 24 using the Role Fitness Test (Entry), which is used by the British Army as a selection standard to confirm the appropriate level of fitness to commence basic training. It involves an isometric mid-thigh pull, seated medicine ball throw, and a timed 2-km run. A vertical jump test will be completed as a military-relevant field-based measure of power. The occupational physical performance tests will be conducted using military equipment and following military procedures (field-expedient measures). As part of military physical performance testing, there is a minimum standard that individuals must achieve, and maximum scores or values are used across these tests. The maximum values will be reported for the occupational physical performance tests in this study.

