**Methods:**

Eligible servicewomen will be assigned to a training or control group in a nonrandomized controlled trial 6 weeks after childbirth. Group allocation will be based on the location of standard pregnancy and postpartum care. The control group will receive standard care, with no prescribed intervention. The training group will start an 18-week core and pelvic health rehabilitation program 6 weeks post partum and a 12-week resistance and high-intensity interval training program 12 weeks post partum. All participants will attend 4 testing sessions at 6, 12, 18, and 24 weeks post partum for the assessment of occupational physical performance, pelvic health, psychological well-being, quality of life, and musculoskeletal health outcomes. Occupational physical performance tests will include vertical jump, mid-thigh pull, seated medicine ball throw, and a timed 2-km run. Pelvic health tests will include the Pelvic Organ Prolapse Quantification system, the PERFECT (power, endurance, repetitions, fast, every contraction timed) scheme for pelvic floor strength, musculoskeletal physiotherapy assessment, the Pelvic Floor Distress Inventory–20 questionnaire, and the International Consultation on Incontinence Questionnaire–Vaginal Symptoms. Psychological well-being and quality of life tests will include the World Health Organization Quality of Life questionnaire and the Edinburgh Postnatal Depression Scale. Musculoskeletal health outcomes will include body composition; whole-body areal bone mineral density; tibial volumetric bone mineral density, geometry, and microarchitecture; patella tendon properties; muscle architecture; muscle protein and collagen turnover; and muscle mass and muscle breakdown. Data will be analyzed using linear mixed-effects models, with participants included as random effects, and group and time as fixed effects to assess within- and between-group differences over time.

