## Discussion

### Hypothesis

We hypothesize that occupational physical performance will improve to a greater extent in the training group, who will receive the combined core reconnection and physical development training intervention, than it will in the control group. We also hypothesize that the training group will see greater improvements in all the secondary outcome measures.

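### Four performance tests are all primary for one global hypothesis, and the protocol does not say which test decides or how many must succeed

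*Protocol article*

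**What the plan says.** The Occupational Physical Performance Overview, under Primary Outcome Measures, describes the Role Fitness Test (Entry): "It involves an isometric mid-thigh pull, seated medicine ball throw, and a timed 2-km run". It adds: "A vertical jump test will be completed as a military-relevant field-based measure of power". The Abstract lists the same four together: "Occupational physical performance tests will include vertical jump, mid-thigh pull, seated medicine ball throw, and a timed 2-km run". None is ranked. All four are measured at weeks 12 and 24.

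The Hypothesis section makes a single claim: "We hypothesize that occupational physical performance will improve to a greater extent in the training group".

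The Statistical Analysis section describes one mixed-model approach for all outcomes, "with group and time included as fixed effects, to assess within- and between-group differences over time", and says the models will establish whether the rates of change in the two groups differ. It sets no significance level.

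The only α is in the Power Calculation, where each comparison is sized "with a 1 − β of .80 and α of .05". Sidedness is not stated. The wording is directional ("identify greater posttraining strength in the intervention group than in the control group"), and the section concludes that "11 participants per group would be sufficient to detect improved strength and aerobic fitness in the intervention group compared with the control group".

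**The concern.** The reader is given four primary results and one conclusion, with nothing to connect them. The protocol could mean that any one test is enough, that all four are needed, or that one of them leads. These readings have very different error rates and power, and the choice stays open until the results are known.

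Mixed results are likely in a trial of this size, so the question will probably arise. The deciding test could then be chosen after the data are seen, in a trial that already has nonrandom allocation and, as its Limitations section says, an unblinded research team.

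The sizing does not settle the matter. It covers strength and aerobic fitness. The jump and the throw, both described as tests of power, have equal primary status but no sizing basis.

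**Working it through.** **Inputs from the protocol.** Four primary tests; α = .05 and power .80 (Power Calculation only); d = 1.23 and 1.10 for single-lift strength, 2.55 and 1.62 for squat and bench press, 3.26 for a 3.2-km run; 11 per group needed, at least 15 recruited.

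**Assumptions.** The protocol gives no correlation between the tests, so a common correlation of 0, 0.5 and 0.8 is used. The sizing effects come from post-training values on related but different tests. They are carried over to the trial's own tests and to differences in change for illustration.

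**Step 1: reproduce the stated sample size.** Two-sample t test, noncentral t, 80% power, α = .05:

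| d | n per group, one-sided | n per group, two-sided | Protocol |
|---|---|---|---|
| 1.23 | 9 | 12 | 9 |
| 1.10 | 11 | 15 | 11 |
| 2.55 | 3 | 4 | 3 |
| 1.62 | 6 | 8 | 6 |
| 3.26 | 3 | 3 | 3 |

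The one-sided test matches every stated figure, so one-sided .05 is the working reading of α.

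**Step 2: any one of four suffices, no true effect.** For independent tests the chance of at least one false claim of improvement is 1 − (1 − α)^4:

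- one-sided .05: 1 − 0.95^4 = 18.5%
- two-sided .05, counting only errors in favour of training: 1 − 0.975^4 = 9.6%, against a nominal 2.5%

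Simulated t tests with 11 per group and equally correlated outcomes (100,000 replicates) give, to within simulation error:

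| Correlation | One-sided .05 | Two-sided .05, favourable direction only |
|---|---|---|
| 0 | 18.4% | 9.7% |
| 0.5 | 14.7% | 7.9% |
| 0.8 | 10.7% | 5.8% |

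**Step 3: all four required.** There is no inflation: with no true effect on any test, the chance that all four reach two-sided .05 is below 0.2% for correlations up to 0.5. The cost is power. With 11 per group, d = 1.10 gives 80.1% power per test one-sided, so four independent tests give 0.801^4 = 41%. If the run has d = 3.26 its power is essentially 100%, so the joint figure is 0.801^3 = 51%. By simulation:

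| Correlation | d = 1.10 on all four | d = 3.26 for the run, 1.10 for the others |
|---|---|---|
| 0 | 41% | 51% |
| 0.5 | 55% | 61% |
| 0.8 | 65% | 68% |

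**Step 4: how often would results be mixed?** With d = 1.10 truly present on every test, 11 per group and one-sided .05, some tests succeed and others fail in 59%, 42% and 27% of trials at correlations 0, 0.5 and 0.8.

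**The case against.** The best defence is that multiplicity rules and testing order usually belong in an analysis plan, that none is shown here, and that this article condenses a fuller protocol. That stands for the mechanics of adjustment, and their absence is not criticised. It does not cover the primary designation. The article states its primary outcomes, sizing, model and hypothesis in full, and names four primaries for one claim.

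It can also be said that the analysis section leans towards estimation, with standardised magnitudes of change and a principal component analysis, and sets no per-test threshold. Judging each test at .05 is therefore an inference from the sizing text. That stands, and the error rates above are conditional on it. Neither the standardisation nor the component analysis is offered as a way to combine the primary tests.

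Four stronger readings are tempting but unsupported:

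- **A single false-claim rate of about 16%.** Two-sided testing at a correlation near 0.5 gives roughly that figure, but it counts errors in both directions, including tests on which training looks worse. It also needs a correlation and an any-one rule that the protocol does not state. A range is all that can be given.
- **The contrast is left open.** The analysis section asks whether the groups' rates of change differ, the hypothesis speaks of greater improvement, and the tests are done only at weeks 12 and 24. The difference in change over that interval is implied.
- **Post-training differences are a second route to success, raising the error further.** The post-training values in the Power Calculation show where the effect sizes were borrowed from. They do not announce another test.
- **No reading can give both α = .05 and 80% power.** If all 15 per group are retained and all four tests are required, one-sided joint power with d = 1.10 throughout is 66%, 74% and 81% at correlations 0, 0.5 and 0.8. The target can be reached at high correlation without dropout, although the protocol itself plans on 11.

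**Conclusion.** The point holds: one global hypothesis, four equally ranked primary tests, and no lead test, order or success rule.

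Its size depends on the rule eventually applied. If any one test suffices at .05, the false-claim rate is about 11% to 19% one-sided, or about 6% to 10% against 2.5% two-sided. If all four must succeed, type I error is controlled, but joint one-sided power with 11 per group is about 41% to 65%, or about 51% to 68% if the run has the protocol's own large effect. These figures rest on assumed common correlations of 0 to 0.8, on the .05 of the sizing text applying to each test, and for power on d = 1.10 for the tests other than the run.

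The jump and throw have primary status without a sizing basis under any rule. The gap should be closed before the results are analysed, but it does not invalidate the design.

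**What to change.** In the Occupational Physical Performance Overview and the Statistical Analysis section:

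1. State that the deciding contrast is the between-group difference in change from week 12 to week 24. This makes explicit what the analysis and hypothesis sections already imply.
2. Make the two outcomes behind the sample size confirmatory, in a fixed sequence at the full α: the 2-km run, then the isometric mid-thigh pull only if the run succeeds. State α and its sidedness.
3. Either continue the sequence with the vertical jump and medicine ball throw, or make them secondary.
4. Label within-group changes as descriptive.

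The run should come first because, at the protocol's d of 3.26, its power with 11 per group is essentially 100%, so the gate costs the strength test almost nothing. With the strength test first at d = 1.10, the run could not be claimed in about 20% of trials one-sided (power 80%) or 31% two-sided (power 69%).

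The change is to wording only, with no added visits, data or participants. The downside is that each later test is confirmatory only if those before it succeed. If the run effect is much smaller than the borrowed figure, the gate costs more. Sharing α equally instead would cost power at once: at .0125 one-sided, power for d = 1.10 falls from 80% to 57% with 11 per group and from 90% to 74% with 15.
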